### Study status

Different sites are at different stages of project implementation including ethical approval pending (Iran); ethical approval obtained and recruiting participants (Somalia) and participant recruitment completed (Indonesia, Iraq, Malaysia, Pakistan and Turkey).

### Recruitment

The mode of recruitment will vary between countries, but will generally involve the distribution of the survey link using a participant mailing list or social media list held by each international collaborator at the host site. The local researchers will be using sampling techniques that are appropriate within their cultures and contexts, which for the most part resemble snowball sampling techniques.

### Procedure

Participants receive a survey link via the recruitment method above. The online survey comprises a participant information sheet, consent form and questionnaires. If a subject consents, they are asked to complete the online survey (which includes the self-report measures described above) using the Qualtrics XM online survey platform. The survey takes approximately 15–20 min to complete and is provided in the appropriate language for the site. Information is provided about local supports that can be accessed if the self-report questions were to cause distress.

### Patient and public involvement

The project has been designed with community and general public involvement. Feedback has also been taken on project design from academics and the general public in the countries of interest.

### Data management

To ensure the anonymity of the obtained dataset the following standard operating procedures are in place. Where applicable, only the international collaborators hold contact information for their participant pool. Each site has specific guidelines to preserve anonymity specified in their local ethics application. Following collection, data will be saved on the University of Otago, New Zealand Qualtrics platform using an auto-generated non-identifiable letter-number string. Importantly, the obtained data set will be completely anonymous as no identifiable information is obtained in the survey.

### Data analysis

Incomplete survey responses will be removed from the analyses. Statistical analyses will be carried out to examine the psychosocial impacts of the COVID-19 pandemic in different countries and provide psychometric evidence using SPSS V.28.0^39^ and Stata Release V.17.^40^ Reporting will follow ‘Strengthening the Reporting of Observational Studies in Epidemiology’ guidelines.^41^

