#### COVID Psychosocial Impacts Scale

This is a novel 32-item measure used to examine the psychosocial impacts of the COVID-19 pandemic. The scale asks participants if they have experienced stressors in response to COVID-19 and then to indicate the magnitude of stress on a 6-point scale scored from 0=‘no’, 1=‘yes, no stress at all’ to 5=‘yes, a lot of stress’. An overall pandemic-related stress score can be calculated ranging from 0 to 160.

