#### Kessler-10

This is a 10-item measure assessing symptoms of psychological distress in the previous 30 days.^34^ Each item is scored from 1=‘none of the time’ to 5=‘all of the time’. The raw score can range from 10 to 50; with scores 30 and above indicating severe mental distress.^36^

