#### WHO Well-Being Index

This is a short 5-item measure assessing subjective psychological well-being in the previous 2 weeks.^35^ Each item is scored from 0=‘at no time’ to 5=‘all of the time’. The raw score range is 0–25; this can be multiplied by 4 to give a final score, with 100 representing the highest subjective well-being rating.

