#### PTSD Checklist for DSM-5

This is a 20-item measure assessing symptoms of PTSD in the past month anchored in response to COVID-19 as a potentially traumatic event. Each item is scored from 0=‘not at all’ to 4=‘extremely’; with a severity score range of 0–80.^37^

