#### Post-traumatic Growth Inventory

This is a 21-item measure assessing change following exposure to trauma,^38^ adapted to reflect how change occurred in your life as a result of COVID-19. There are five subscales (relating to others, new possibilities, personal strength, spiritual change and appreciation of life). Each item is scored from 0=‘not at all’ to 5=‘a lot’ with a score range of 0–105, with higher scores reflecting positive transformation after the traumatic event.

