#### Sample size estimation

As no prevalence of the psychosocial impacts of the COVID-19 pandemic in the general population of the countries of interest exists, no formal sample size calculations were conducted. The final target sample size of n=500 per country was pragmatically selected balancing the competing demands of maximising statistical power, expedited cost-effective data collection processes and international reach while simultaneously minimising institutional burden.^42^

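### Removing every incomplete survey from all analyses throws away finished scales and can bias distress estimates and country comparisons

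*Protocol article*

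**What the plan says.** The Data analysis section opens with the rule "Incomplete survey responses will be removed from the analyses". Nothing there or in the subsections that follow restricts it to a scale, a model or a pattern of missingness, and the article does not say what makes a response incomplete.

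The rule applies to a survey with five scales:

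- CPIS: "This is a novel 32-item measure used to examine the psychosocial impacts of the COVID-19 pandemic"
- K10: "This is a 10-item measure assessing symptoms of psychological distress in the previous 30 days"
- WHO-5: "This is a short 5-item measure assessing subjective psychological well-being in the previous 2 weeks"
- PTSD checklist: "This is a 20-item measure assessing symptoms of PTSD in the past month anchored in response to COVID-19"
- Growth inventory: "This is a 21-item measure assessing change following exposure to trauma"

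Sociodemographic and prior-trauma questions come on top. Under Procedure, the survey is online and self-completed, and "The survey takes approximately 15–20 min to complete". The same section provides details of local support in case the questions upset respondents.

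The planned analyses differ in what they need. Psychometric analyses plans reliability for each measure separately, and a correlation matrix of CPIS with WHO-5 and K10. The within-subjects and between-subjects sections plan models by site and across countries. The Discussion accepts that response will differ between countries and relies on multi-level modelling to mitigate the design's limitations.

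**The concern.** A single deletion rule ties every analysis to completion of the whole survey. Someone who answered all of the K10 but left part of the growth inventory blank is lost to the K10 analysis, although that analysis does not use the growth inventory. Data already collected and usable are discarded.

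The second risk is bias. A 15 to 20 minute unsupervised survey about trauma and distress may be abandoned more often by some people than others. If completion is related to distress, completers' means and prevalences differ from those of everyone who took part. If that relation or the completion rate differs by country or language version, part of an apparent country difference in distress may be a difference in who finished. Country comparison is a stated aim, so this matters.

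The remedy the Discussion names does not reach the problem. Deleted records never enter the multi-level models. Each person contributes one survey, so there are no repeated measurements from which a mixed model could recover them.

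**Working it through.** The article gives no completion rate or allowance for non-completion, so there is no figure of the plan's own to reproduce. The check has four steps.

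**1. Item count.** From the Measures section: 32 + 10 + 5 + 20 + 21 = 88 scale items. The validity analysis of CPIS with K10 and WHO-5 needs 32 + 10 + 5 = 47 of them. Reliability of the K10 needs 10.

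**2. Loss if items can be skipped.** Assume that one blank anywhere deletes the record and that each item is left blank independently with probability m. The share of records complete on k items is (1 − m)^k. The documents give no m; 0.1% to 1% is an assumed range.

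- All 88 items: 0.999^88 = 0.916; 0.995^88 = 0.643; 0.99^88 = 0.413.
- K10 alone: 0.999^10 = 0.990; 0.995^10 = 0.951; 0.99^10 = 0.904.

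Per 500 people starting the survey (500 serves only as a convenient base):

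| m | All 88 items | CPIS + K10 + WHO-5 (47) | CPIS (32) | K10 (10) | WHO-5 (5) |
|---|---|---|---|---|---|
| 0.1% | 458 | 477 | 484 | 495 | 498 |
| 0.5% | 322 | 395 | 426 | 476 | 488 |
| 1% | 206 | 312 | 362 | 452 | 475 |

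The first column is what the rule keeps for every analysis. The others are what each analysis could keep. If blanks cluster within people, fewer records are lost than shown.

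**3. Loss if every item is forced.** Gaps then arise only by break-off. If a share f breaks off and a share g of those had already finished the scale of interest, the rule keeps 1 − f, while an analysis by measure keeps 1 − f + f·g. With f = 20% (assumed), that is 80% against anything from 80% (g = 0) to 100% (g = 1). The article gives neither the order of the scales nor a forced-response setting, so g is unknown.

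**4. Bias.** Let d be the mean distress of deleted respondents minus that of completers, in SD units. The completer mean minus the mean of all participants is −f·d.

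- d = 0: no bias at any f.
- f = 20%, d = +0.3: −0.20 × 0.3 = −0.06 SD; with d = −0.3, +0.06 SD.
- f = 40%, d = +0.3: −0.40 × 0.3 = −0.12 SD; with d = −0.3, +0.12 SD.

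For two countries A and B, the error in the difference of means (A minus B) is −(f_A·d_A − f_B·d_B). It vanishes only if the two products are equal. Every f and d here is assumed. Regression coefficients are less exposed: they are biased only if completion depends on the outcome after allowing for the covariates in the model.

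**The case against.** The strongest case against is that the documents establish no bias. A reader might infer that distress is underestimated, because distressed people seem likelier to stop. The article gives no completion rate, mechanism or direction, and bias is zero if completion is unrelated to distress. A simulated shortfall in K10 points would only return its own assumptions. This stands: the rule can bias the estimates, and no more can be said.

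A reader might also infer that the analysed sample must fall short of the target. Sample size estimation says only that "The final target sample size of n=500 per country was pragmatically selected". It does not say whether the 500 are starters or completers; if completers, there is no shortfall.

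Third, incomplete may mean a survey not submitted, not one with a single blank. The figures in step 2 would then not apply, and what could be recovered would depend on scale order. This also stands, and is why those figures are illustrations. It does not rescue the rule, which under either reading removes any finished scale in a partial record.

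Finally, the authors already disclose non-systematic recruitment and decline to generalise to national populations. That lowers the weight of the point, since deletion adds to selection already admitted. It does not justify a further, avoidable loss, and the Discussion does not mention deletion of partial responses.

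**Conclusion.** The point holds in a limited form. The article states a current and unrestricted rule; it is not a detail left to an analysis plan. Followed as written, it discards finished K10, WHO-5 or CPIS data whenever another part of the survey is unfinished. It can bias distress means, prevalences and country comparisons if completion is related to distress or differs by country, and the planned multi-level models cannot repair that.

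The loss of data follows from the rule itself wherever a partial record contains a finished scale. Its extent is not known. The contrast of 92% to 41% fully complete records with 99% to 90% for the K10 alone rests on three assumptions: items can be skipped, skips are independent at 0.1% to 1%, and one blank deletes the record. Neither the size nor the sign of any bias can be derived from the documents.

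**What to change.** Replace the sentence in Data analysis along these lines:

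> Each analysis will include every respondent with the scales and covariates it requires. Completeness is defined separately for each scale. The analysis restricted to fully complete surveys will be reported as a sensitivity analysis. Multiple imputation within country, using answered scales and demographics, will be a further sensitivity analysis.

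Add that completion will be reported by country, and that completers will be compared with partial responders on the scales both groups answered. This would give the first evidence on whether completion is related to distress.

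The definition of completeness should suit each scale. CPIS items record separate events, with zero meaning that the event did not happen, so filling a blank with the person's average over other events is not recommended.

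No new data collection is needed, which matters because Study status reports recruitment finished in five of the seven countries. The costs are modest extra analysis, a sample size that varies between analyses and must be reported for each, and a missing-at-random assumption for the imputation. The change also depends on partial records having been retained, which the article does not say. If they were not, the article should say so, and the results should be described as those of completers only.

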#### Sample size estimation

As no prevalence of the psychosocial impacts of the COVID-19 pandemic in the general population of the countries of interest exists, no formal sample size calculations were conducted. The final target sample size of n=500 per country was pragmatically selected balancing the competing demands of maximising statistical power, expedited cost-effective data collection processes and international reach while simultaneously minimising institutional burden.^42^

#### Psychometric analyses

Reliability analyses will be carried out on each measure to determine the suitability of its use, employing item-total correlations and Cronbach’s α as a measure of internal homogeneity and consistency. The construct validity of CPIS with WHO-5 and K10 will be examined using a correlation matrix.

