To address the issues identified above, we developed the 50-item COVID Psychosocial Impacts Scale (CPIS) to comprehensively assess the impacts of the pandemic including the adverse personal, social and economic consequences that followed. The construction of the scale was informed by our team’s experience assessing the psychosocial impacts of the Canterbury Earthquakes^28 29^ and the Mosque Attacks in 2019.^30^ Notably, the existing pandemic-related scales were also consulted in scale development.^6 16–20^ The items and subscales of CPIS were modelled on the Social Readjustment Scale^31^ assessing exposure to pandemic-related life events (disruptions to personal, family, employment, faith, education and daily routines) and the resultant level of stress. It also included questions examining the potential positive consequences of the COVID-19 pandemic. The CPIS was refined using the ‘group mind’ process,^32^ with colleagues from a range of countries and cultures (Bangladesh, Ghana, Pakistan and Turkey) reviewing a draft of the questionnaire, with iterative improvements based on their comments. The applicability of the CPIS for use in a range of countries and cultures was duly considered through collaboration with international colleagues.

The 50-item CPIS has been validated in a non-representative New Zealand sample at two-time points (2020, 2022) when the population exposure to COVID-19 community infections varied markedly.^33^ In that study, the CPIS was administered with a measure of psychological distress (Kessler Psychological Distress Scale, K10)^34^ and well-being (WHO Well-Being Index, WHO-5).^35^ Findings indicate a unidimensional structure within CPIS subscales while it correlates with psychological distress and general well-being is not only a proxy for these constructs.^33^ Based on findings from the validation study, we found that some items were less important in future iterations of the CPIS. Therefore, we have refined CPIS from 50 to 32 items.

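### CPIS construct validity is checked only against two general scales, so the plan yields no convergent evidence for pandemic impact although two COVID-19-anchored scales are collected

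*Protocol article*

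**What the plan says.** The CPIS section describes the construct: "The scale asks participants if they have experienced stressors in response to COVID-19 and then to indicate the magnitude of stress on a 6-point scale". The article gives no look-back period for it.

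For validity, the Psychometric analyses section says: "The construct validity of CPIS with WHO-5 and K10 will be examined using a correlation matrix". The Discussion describes the same comparison, with well-being and distress measures only. No expected size or direction is given.

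The four companion scales are described under Measures:

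- K10: "This is a 10-item measure assessing symptoms of psychological distress in the previous 30 days". No COVID-19 anchor is stated.
- WHO-5: "This is a short 5-item measure assessing subjective psychological well-being in the previous 2 weeks". No COVID-19 anchor is stated.
- PCL-5: "symptoms of PTSD in the past month anchored in response to COVID-19 as a potentially traumatic event".
- Post-traumatic Growth Inventory: "adapted to reflect how change occurred in your life as a result of COVID-19".

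The section on within-subjects analyses lists post-traumatic stress and growth as study variables. Neither is named anywhere as a criterion for CPIS validity.

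On the earlier New Zealand validation of the 50-item version, which used K10 and WHO-5, the Introduction reports: "Findings indicate a unidimensional structure within CPIS subscales while it correlates with psychological distress and general well-being is not only a proxy for these constructs".

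**The concern.** The study presents the CPIS as a measure of pandemic-related events and the stress they caused, and it offers psychometric evidence on the scale in several countries as a main contribution. Convergent evidence for such a construct needs at least one criterion that is itself tied to the pandemic. K10 and WHO-5 measure general state. They can show how much of the CPIS is shared with distress and well-being, but not what the unshared part is. That part could be pandemic impact, or it could be some other stable source of variance, such as a tendency to endorse complaints.

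At stake is the claim that the translated 32-item version measures pandemic impact in each country. The stated analysis would support only a weaker claim, that it is related to distress without being identical to it.

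**Working it through.** The article states no calculated figure on this point, and the 500 per country is described as pragmatic. There is nothing to reproduce, so the check is an illustration.

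**Input from the article.** n = 500 per country.

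**Assumptions (not in the article).** Independent standardised factors: mood, pandemic impact, and unrelated reliable variance. Loadings on mood: K10 0.90, WHO-5 -0.85, PCL-5 0.75. PCL-5 loading on pandemic impact: b, from 0 to 0.5. Three versions of the CPIS have nearly the same reliability:

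- A, mood 0.55 and pandemic impact 0.70: reliability 0.55² + 0.70² = 0.79
- B, mood 0.55 and unrelated variance 0.70: reliability 0.79
- C, mood only, 0.89: reliability 0.89² = 0.79

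**Step 1: the planned correlations.** Each correlation is the sum of products of loadings.

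- A and B with K10: 0.55 × 0.90 = 0.50. With WHO-5: 0.55 × (-0.85) = -0.47.
- C with K10: 0.89 × 0.90 = 0.80. With WHO-5: 0.89 × (-0.85) = -0.76.

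The Fisher interval is tanh(atanh(r) ± 1.96/√497). It gives 0.43 to 0.56 for r = 0.50 and 0.77 to 0.83 for r = 0.80. The reliability ceiling for CPIS with K10 is √(0.79 × 0.81) = 0.80. So the planned matrix separates C, which sits at the ceiling, from A and B, which sit well below it. It cannot separate A from B at any sample size, because their correlations are identical.

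**Step 2: adding PCL-5.** The mood variance left after K10 and WHO-5 is 1/(1 + 0.81/0.19 + 0.7225/0.2775) = 0.127. The residual variance of PCL-5 is 0.5625 × 0.127 + 0.4375 = 0.509. That of A and of B is 0.3025 × 0.127 + 0.6975 = 0.736. The square root of the product of these two is 0.612.

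- A: partial r = (0.55 × 0.75 × 0.127 + 0.70b)/0.612. This is 0.31 at b = 0.2 and 0.66 at b = 0.5. The plain correlation is 0.4125 + 0.70b, or 0.55 to 0.76.
- B: partial r = (0.55 × 0.75 × 0.127)/0.612 = 0.09. The plain correlation is 0.41.
- At b = 0, A and B coincide again (0.41 and 0.09).

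**Step 3: can significance of the partial correlation serve as the test?** For C the residual variance is 0.7921 × 0.127 + 0.2079 = 0.309, and the partial r is (0.89 × 0.75 × 0.127)/√(0.309 × 0.509) = 0.21. With standard error 1/√(500 - 2 - 3) = 0.045 on the Fisher scale, this is significant at the two-sided 5% level with probability above 0.99. For B it is significant about half the time. Neither version has any pandemic content. The cause is the 12.7% of mood variance that K10 and WHO-5 leave unadjusted. The 95% interval for C (0.13 to 0.30) also overlaps that for A at b = 0.2 (0.23 to 0.39), so the partial correlation has to be read together with the K10 correlation from Step 1.

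**The case against.** A reader might infer that the planned test cannot show the CPIS to be more than present mood. The documents do not support that. Cronbach's α is planned in the same section, so a K10 correlation can be set against its reliability ceiling, and a value well below it would show distinctness. Step 1 illustrates this, and the Introduction reports that reading for the 50-item version.

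A reader might also argue that the 2-week and 30-day windows disqualify WHO-5 and K10, since pandemic stress may have come earlier. That gives no reason to prefer PCL-5, which covers the past month as well. Its advantage is the anchor, not the window. It remains a symptom scale, and it helps only as far as the anchoring captures something specific to the pandemic (b above 0).

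Finally, correlating a new scale with established distress and well-being scales is a coherent step. The two sections that describe it agree, and a condensed article may leave extra comparators to a fuller plan. Nothing bars the team from reporting more. This limits the weight of the point but does not remove it: the article itself names the comparators, names only two, and describes the same restriction in the Discussion.

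**Conclusion.** The point holds in limited form. As stated, the validity analysis covers association with, and possibly distinctness from, current distress and well-being. It provides no convergent evidence for pandemic impact, although two of the four companion scales are tied to COVID-19. The New Zealand result does not fill the gap: as reported, it concerns the 50-item version and the same two comparators, and it speaks to distinctness.

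The size depends on assumed loadings. Under them, two quite different scales look the same on the planned matrix (0.50 and -0.47), and adding PCL-5 separates them (partial r 0.31 to 0.66 against 0.09) only if it carries pandemic-specific variance. One result does not depend on the particular values: whenever K10 and WHO-5 measure mood imperfectly, and both CPIS and PCL-5 load on it, some positive partial correlation remains without any pandemic content.

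**What to change.** In Psychometric analyses:

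1. Extend the per-country matrix to CPIS, K10, WHO-5, PCL-5 and the Post-traumatic Growth Inventory, keeping K10 and WHO-5 in the main matrix.
2. State expected directions and approximate sizes beforehand. For the growth inventory, take into account that the Introduction describes questions on positive consequences in the CPIS, and say whether any are among the 32 items. Its correlation is therefore not a simple check that the CPIS avoids positive change.
3. Read the K10 and WHO-5 correlations against the ceiling set by the scales' α values, as evidence of distinctness.
4. Report the partial correlation of CPIS with PCL-5 given K10 and WHO-5 as an estimate with its interval. Do not treat significance alone as validity.

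The cost is a few sentences and slightly more analysis per country. All the scales are already in the survey. Recruitment is reported complete in five of the seven countries, and this change does not touch data collection. The downside is that the validity evidence may come out weaker in some countries.
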